### Analysis plan

Baseline characteristics will be summarised using means and standard deviations or frequencies and percentages as appropriate. The primary outcome variable will be the BRIEF-A GEC score and the effect of the intervention will be estimated using a linear mixed model. The model will include the baseline BRIEF-A GEC as a covariate and a fixed effect for each time period after baseline to account for any secular trends. We will also include random effects for treatment centre, time within centre and individual within centre to account for the clustering, repeated measurements on centre and repeated measures on individuals, respectively. The main predictor of interest will be a pre−/post-intervention variable, which will measure the overall effect of the intervention. The data will be analysed according to the intent-to-treat principle, with sensitivity analysis undertaken to include all participants under an appropriate multiple imputation model for the missing data.

Two analyses are proposed to investigate the impact of CR on treatment retention, being:Direct analysis of retention (proportion of time spent in treatment relative to program duration) across TAU and CR conditions; andComparison of historical retention data (dating back 2–5 years) with retention rates following the first CR phase for each site. A 10% increase in service retention rate will be the indicator of a clinically meaningful gain.

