## Background

Substance use disorder (SUD) is a major global health problem, which has increased notably in the last few years [1]. In Australia, a recent publication reported that one in 200 people in the general population received treatment for substance use in 2014–15, which represents a 6% increase from the previous year [2]. Although SUD is frequently described as a chronic and relapsing condition, favourable long-term outcomes are consistently associated with alcohol and other drug (AOD) treatment completion [3]. However, failure to complete treatment, or “drop-out”, is very common in both inpatient and outpatient treatment services [4, 5].

According to a systematic review of the literature, one of the major risk factors of drop-out from AOD treatment is cognitive impairment [6]. Over the last two decades, neuropsychological research has consistently shown that substance use is associated with a significant degree of impairment in cognitive functioning. Whilst specific aspects of cognitive functioning may predate and influence the initiation of AOD use [7], increased substance use results in a greater degree of impairment [8, 9]. That is, there is a strong association between the quantity and duration of AOD use and the degree of cognitive dysfunction. Cognitive deficits in individuals with SUD may be further exacerbated by the presence of common comorbidities such as traumatic brain injury and psychiatric disorders [10, 11]. Although partial recovery of cognitive impairment may occur after immediate cessation of AOD use, many cognitive deficits fail to recover following withdrawal and abstinence [12, 13]. For example, it has been estimated that approximately 50–80% of recently detoxified individuals with SUD are cognitively impaired when assessed with the Montreal Cognitive Assessment [14–17].

In individuals with SUD, the most prominent cognitive deficits are seen in executive functioning (EF) [9, 18]. EF abilities (such as working memory, planning and organisational skills, reasoning, and self-regulation) are mediated by the frontal cortex, an area of the brain that is particularly vulnerable to substance-related impairment [19]. Common AOD treatment interventions, including counselling and psychoeducation, are heavily reliant on intact EF abilities in order to identify, promote and achieve successful behavioural change [20, 21]. Thus, EF impairment significantly predicts treatment drop-out and relapse [22–24].

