## Methods/design

### Study setting

The research program will be conducted at ten residential treatment facilities run by non-governmental organisations in NSW, Australia. All organisations will be abstinence-based however a portion of residents may be prescribed medications or opioid substitution treatments (OST) (e.g. methadone). Limited leave from the residential facilities, close observation by staff and other residents, and random urine tests will ensure abstinence from substances while participants are enrolled in treatment programs. Services that accommodate at least 15 residents and have a minimum project duration of 10 weeks will be invited to participate in the study.

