Site 8		TAU 1		TAU 2		TAU 3		Cog Rem 1		F/U Period	
Site 9		TAU 1		TAU 2		TAU 3		Cog Rem 1		F/U Period	
Site 10		TAU 1		TAU 2		TAU 3		Cog Rem 1		F/U Period	

Note: *Cog Rem* Cognitive Remediation Phase, *TAU* Treatment-As-Usual Phase, *F/U Period* Follow Up Period

The estimated number of participants is based on prior research in NSW residential drug and Alcohol Treatment [42]. *Discharge* refers to the discharge of participants from the residential treatment service (either through completing the program or self-discharge/drop out before the completion of the program). *Attrition* refers to drop-out from the study or otherwise being non-contactable following discharge from the treatment service.Each site will start with *n* = 20 participants on average;Within a single cohort, there will be:a 40% discharge rate over each six-week TAU/CR phase plus two-week test phase;a 65% discharge rate over the following 2 months;an 80% discharge rate over the following 4 months;a 90% discharge rate over the following 6 months; anda 95% discharge rate over the following 8 months;New clients will enter a service at the same rate as other clients leave the service;If a client enters a service during a TAU/CR phase, they will delay their participation in the trial until the next test phase;Some clients will participate in more than one CR phase;All participants who have completed at least one TAU/CR phase will be eligible for follow-up testing, which will occur at test phases 3, 4, 5 and 6.If a participant has had a CR phase they are ineligible for TAU follow-up.If a participant has had more than one CR phase they will still be eligible for CR follow-upFollow-up attrition rates have been estimated to be:65% attrition at two-month follow up75% attrition at four-month follow up85% attrition at six-month follow up90% attrition at eight-month follow up

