### Intake measures

The following data will be gathered on intake in the form of a structured questionnaireAge;Highest level of educational attainment;Employment status;Marital status;Number of Children/DependentsPrimary substance of misuse;Years of regular use (by substance);Nicotine UseUse of OSTRelapses in residential treatment;Relapses in community treatment;Abstinence duration;Country of birthFirst languageAustralian/Torres Strait Islander StatusReferral source (e.g. self-referred or court-ordered enrolment)

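### The primary BRIEF-A model leaves out abstinence duration, which is already collected at intake; this may cost a little precision but does not cause bias

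*Protocol article*

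**What the plan says.** The Analysis plan section of the protocol article sets out a linear mixed model for BRIEF-A GEC. On fixed effects: "The model will include the baseline BRIEF-A GEC as a covariate and a fixed effect for each time period after baseline". The period effects are there to absorb secular trends, and a pre/post-intervention indicator carries the treatment effect. On random effects: "We will also include random effects for treatment centre, time within centre and individual within centre". No other covariate is named.

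Four other places bear on this.

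- Intake measures lists "Abstinence duration" among the questionnaire items. The article gives it no part in the analysis.
- Background: "Although partial recovery of cognitive impairment may occur after immediate cessation of AOD use, many cognitive deficits fail to recover following withdrawal and abstinence".
- Study setting says of the sites that "random urine tests will ensure abstinence from substances while participants are enrolled in treatment programs", so time in residence adds abstinence under both conditions.
- Study design, below Table 1, assumes 40% discharge over each phase and that "New clients will enter a service at the same rate as other clients leave the service". It also says that some clients will take part in more than one cognitive remediation (CR) phase.

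**The concern.** Any recovery after stopping use follows each person's own time since last use. The model's only time adjustment is calendar period, which is a different clock. With turnover of about 40% per phase, recent arrivals and longer-stay residents sit in the same site and period and receive the same period effect. Baseline GEC records where a person starts, which is not necessarily how much further change to expect.

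If abstinence duration predicts post-phase GEC after baseline GEC is accounted for, that variation stays in the residual and widens the standard error of the CR effect. The trial has ten clusters, and a covariate that is already collected could recover part of the loss.

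**Working it through.** **1. The plan's own figures.** Inputs from Sample size estimation: difference 2.25, SD 5.15, 80% power, 5% significance (two-sided assumed), ICC 0.05, 20 per cluster, cluster autocorrelation 0.5. Table 1 gives three steps.

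- Individually randomised total: 4 × [5.15 × (1.960 + 0.842) / 2.25]² = 164.5, so 165, as stated.
- Clustering: 1 + 19 × 0.05 = 1.95, as stated.
- Repeated assessment: r = 20 × 0.05 × 0.5 / 1.95 = 0.256. With k = 3, 3k(1 − r)(1 + kr) / [(k² − 1)(2 + kr)] = 0.534, as stated.
- Clusters: 165 × 1.95 × 0.534 / 20 = 8.6, so nine, as stated. Ten are recruited.

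There is no numerical error here.

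**2. Power with the ten-site layout.** I used the generalised least squares variance of the CR effect for Table 1 (3, 3 and 4 sites crossing over, four periods, period fixed effects).

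- Total variance: 5.15² = 26.52.
- Between-cluster part: 0.05 × 26.52 = 1.33, split equally by the autocorrelation of 0.5 into 0.66 for cluster and 0.66 for cluster-period.
- Individual part: 0.95 × 26.52 = 25.20, divided by m, the number of scores per site-phase.
- Power = Φ(2.25/SE − 1.96).

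I took m = 20 (the planned size) and m = 12 (20 less the 40% discharge). Repeated scores on one person are treated as independent given the cluster terms, which is a simplification.

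**3. Assumed strength of abstinence duration.** The documents give no figure, so I used a range. Suppose that, given baseline GEC, recent arrivals (40%) improve by d points more per phase than the rest. This contributes 0.4 × 0.6 × d² = 0.24d² to the variance:

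- d = 1: 0.24 / 26.52 = 0.9%
- d = 2.25 (as large as the planned CR effect): 1.215 / 26.52 = 4.6%
- d = 4.5 (twice the planned effect): 4.86 / 26.52 = 18.3%

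**4. Results.** The individual part is multiplied by one minus the share explained.

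| Share explained | SE, m = 20 | Power, m = 20 | SE, m = 12 | Power, m = 12 |
|---|---|---|---|---|
| 0 (model as stated) | 0.741 | 85.9% | 0.869 | 73.5% |
| 0.9% | 0.739 | 86.1% | 0.867 | 73.8% |
| 4.6% | 0.731 | 86.8% | 0.856 | 74.8% |
| 18.3% | 0.701 | 89.5% | 0.814 | 78.9% |

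**5. Chance imbalance is not an extra loss.** Chance variation in the share of recent arrivals moves a 12-person site-phase mean by an SD of √(1.215/12) = 0.32 points at d = 2.25, or √(4.86/12) = 0.64 at d = 4.5. This is the variance from step 3 averaged over 12 people, so it is already in the standard errors above. For scale, the sample-size assumptions allow a cluster-period SD of √0.663 = 0.81.

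**The case against.** The strongest case against raising this is that the model is a conventional stepped wedge model. The article says what the model will include without saying that nothing else enters, and an analysis plan that is not shown may list further covariates. That stands as a reason to rank the point low. The article does nevertheless write the model out term by term, and the suggestion concerns those terms.

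The premise is also weaker than it may look. A reader might infer that the article says cognition recovers with abstinence. It says only that partial recovery may occur, and adds that many deficits persist. That passage concerns cognitive impairment, illustrated by a screening test, whereas the primary outcome is a self-report inventory. Strengths and limitations says that the two kinds of executive function measure are minimally correlated. So the documents do not establish that GEC change depends on time since last use once baseline GEC is known. This stands, and it is why the lower end of the range cannot be ruled out.

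A reader might also infer that unmodelled recovery biases the CR estimate. The documents do not support that. Sites are randomised to sequence, and period effects with concurrent treatment-as-usual sites remove average recovery. Baseline GEC and the individual random effect may absorb part of what remains. Nor is planned power overstated on this account: the SD of 5.15 comes from earlier data in the same kind of setting, so variation in recovery in those data is already in it.

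Finally, the contrast between arrivals and stayers is only a proxy for abstinence. Clients who arrive mid-phase wait for the next test phase and may already have spent weeks abstinent, and few residents are projected to stay for many months.

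**Conclusion.** The point holds as a low-severity improvement. The stated model does not use a pre-exposure covariate that the trial already collects and that the article gives some reason to think prognostic. The consequence is a possible small loss of precision.

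The gain from adding it runs from about 0.2 points of power (share about 1%, 20 scores per site-phase) to about 5.4 points (share about 18%, 12 scores per site-phase). The upper end requires recent arrivals to out-improve other residents by twice the planned treatment effect, so a gain near the lower end is easier to credit. All of these gains rest on the assumed share. The layout, SD, ICC and autocorrelation are the article's own.

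The fall from 85.9% to 73.5% comes from having 12 rather than 20 scores per site-phase. It is not caused by omitting this covariate.

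**What to change.** Add one prespecified fixed covariate to the primary BRIEF-A model: log-transformed abstinence duration measured before any CR exposure, either at intake or at the participant's first pre-phase assessment. State which of the two is used, and fix the choice before outcome data are seen. Leave baseline GEC, the period effects and the random effects as they are.

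Do not update the covariate at later phases. For someone entering a second or third CR phase, accumulated abstinence is measured after exposure and depends on staying in treatment. Retention is itself a primary outcome that CR is expected to improve, so adjusting for an updated value could remove part of the effect or introduce selection.

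The cost is a line of text, one degree of freedom and a rule for missing intake values. No new data are needed.

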## Discussion

EF impairment is a significant predictor of treatment drop-out for individuals with SUD. There is an opportunity for AOD treatment providers to address cognitive impairment as part of routine care in order to potentially increase treatment efficacy and reduce treatment drop-out. The present study aims to examine the effectiveness of providing a group-based compensatory CR intervention as an adjunct to residential AOD treatment programs. It is expected that compared to pre-intervention, participants will demonstrate a significant improvement in EF and the duration of treatment retention. In addition, it is anticipated that there will be reductions in harmful AOD use and associated health service utilisation, as well as significant improvements in personal goal achievement, quality of life, and treatment satisfaction. As the current study is the first stepped wedge cluster randomised trial of a compensatory CR intervention within a residential AOD population, the results potentially hold important implications for the way that interventions are delivered across treatment settings.

### Strengths and limitations

The current study is a large, multi-site, stepped wedge cluster randomised trial that will be conducted across ten residential treatment programs. The strength of conducting this type of “real world” research is that it is more representative of actual clinical practice and helps to provide some evidence regarding the feasibility of using these types of interventions as part of ongoing routine care. The research design also includes additional attempts to increase the ecological validity of the results by using very inclusive eligibility criteria, including individuals with previous traumatic brain injuries and psychiatric comorbidities.

Another strength of the study is that outcome measures have been carefully chosen to reflect the effects of CR on real-world functioning. Given that performance- and inventory-based EF assessments are minimally correlated and may assess distinct components of EF, the current study aims to provide a comprehensive assessment of EF to account for abilities that are likely to translate to functional outcomes [36, 76]. This study will also be the first to evaluate whether compensatory CR will result in improved treatment retention, which has been shown to be an important predictor of successful long-term outcomes for individuals with SUD [3]. Furthermore, the current study will take person-centred outcomes into account, including measurements of AOD use, health service use, personal goal attainment, quality of life, and treatment satisfaction. Inclusion of person-centred outcomes will measure whether CR is likely to result in contextually meaningful and desired treatment outcomes. Finally, an economic analysis will be undertaken to determine the cost of delivering CR versus TAU in residential treatment settings.

A significant challenge in this trial is the high rate of unplanned drop-out that is common in residential AOD treatment services. According to recent figures, approximately 20% of individuals with SUD unexpectedly cease treatment [2]. To help address this concern, compensatory CR will be delivered in one-hour sessions, twice a week, over a six-week period, which is a reasonable amount of time to expect individuals to dedicate to the intervention. A further challenge will be retaining participants at follow-up. Attempts to improve follow-up rates in the current study include using telephone and online follow-up to administer some outcome assessments, obtaining contact details of significant others to help with locating participants and reinforcing the importance of conducting follow-up to participants.

The current study will be the first stepped wedge cluster randomised trial of a compensatory CR intervention in a residential substance abuse population. The study seeks to address a significant gap in the literature by examining the effectiveness of implementing a six-week CR group program within AOD residential treatment programs. It is expected that following completion of CR, participants will demonstrate significantly improved EF and treatment retention rates, reduced AOD use and health service utilisation rates, as well as achievement of individually-set goals, quality of life, and treatment satisfaction.

## Abbreviations

AOD: Alcohol and other drugs
ATOP: Australian Treatment Outcomes Profile
BEAT: Brief executive assessment tool
BRIEF-A: Behavioural rating inventory of executive function – adult version
BSCS: Brief Self Control Scale
CRiDAS: Cognitive Remediation in Drug and Alcohol Services
DACIST: Drug and Alcohol Cognitive Impairment Screening Tool
EF: Executive functioning
EQ-5D: EUROQOL-EQ-5D-5L
EUROHIS-QOL 8: EUROHIS-QOL 8-item index
GAS 2.0: Goal attainment scaling 2.0
GAS: Goal attainment scaling
GEC: Global executive composite
GMT: Goal Management Training
GSRS: Group Session Rating Scale
K10 +: Kessler Psychological Distress Scale Plus
MINI: Mini international neuropsychiatric interview
OST: Opioid Substitution Therapy
PROMIS Global-10: Patient Reported Outcomes Measurement Information System Global 10
Q-LES-Q-SF: Quality of Life Enjoyment and Satisfaction Questionnaire – Short Form
QOL: Quality of Life
SDMT: Symbol Digit Modalities Test
SDS: Severity of Dependence Scale
SUD: Substance use disorder
TAU: Treatment as usual
